## Abstract

**Background:**

Hypertension and diabetes are among the most common and deadly chronic conditions globally. In India, most adults with these conditions remain undiagnosed, untreated, or poorly treated and uncontrolled. Innovative and scalable approaches to deliver proven-effective strategies for medical and lifestyle management of these conditions are needed.

**Methods:**

The overall goal of this implementation science study is to evaluate the **I**ntegrated **T**racking, **R**eferral, **E**lectronic decision support, and **C**are coordination (I-TREC) program. I-TREC leverages information technology (IT) to manage hypertension and diabetes in adults aged ≥30 years across the hierarchy of Indian public healthcare facilities. The I-TREC program combines multiple evidence-based interventions: an electronic case record form (eCRF) to consolidate and track patient information and referrals across the publicly-funded healthcare system; an electronic clinical decision support system (CDSS) to assist clinicians to provide tailored guideline-based care to patients; a revised workflow to ensure coordinated care within and across facilities; and enhanced training for physicians and nurses regarding non-communicable disease (NCD) medical content and lifestyle management. The program will be implemented and evaluated in a predominantly rural district of Punjab, India. The evaluation will employ a quasi-experimental design with mixed methods data collection. Evaluation indicators assess changes in the continuum of care for hypertension and diabetes and are grounded in the Reach, Effectiveness, Adoption Implementation, and Maintenance (RE-AIM) framework. Data will be triangulated from multiple sources, including community surveys, health facility assessments, stakeholder interviews, and patient-level data from the I-TREC program’s electronic database.

**Discussion:**

I-TREC consolidates previously proven strategies for improved management of hypertension and diabetes at single-levels of the healthcare system into a scalable model for coordinated care delivery across all levels of the healthcare system hierarchy. Findings have the potential to inform best practices to ultimately deliver quality public-sector hypertension and diabetes care across India.

**Trial registration:**

The study is registered with Clinical Trials Registry of India (registration number CTRI/2020/01/022723). The study was registered prior to the launch of the intervention on 13 January 2020. The current version of protocol is version 2 dated 6 June 2018.

## Contributions to the literature

The Government of India, beholden to its population of 1.3 billion, has developed an electronic “NCD Portal” that consists of an electronic case record form (eCRF) to manage non-communicable diseases (NCDs) within the government sector. The I-TREC program builds on the eCRF by integrating a proven-effective clinical decision support system for hypertension and diabetes care, accompanied by clinical training, to assist with patient management.We describe the evaluation protocol for the I-TREC multi-component strategy to improve diabetes and hypertensions care at all levels of the four-tier healthcare system in India.Lessons learned may inform optimal approaches to improve healthcare processes and health outcomes within the public sector healthcare system in India and in other similar settings.

## Background

Hypertension and diabetes together affect over 275 million Indians and their families [1]. These conditions are rising rapidly in all regions of India, commonly co-occur [2–4], and are associated with several adverse health outcomes—such as higher rates of death, myocardial infarction, stroke, blindness, kidney failure. Yet, both hypertension and diabetes are treatable such that timely and appropriate therapy mitigates associated morbidity due to complications and premature mortality. While lack of diagnosis is among the major obstacles to seeking appropriate treatment [5, 6], treatment outcomes even after diagnosis are far from ideal. Less than half of individuals who have hypertension and diabetes in the community are aware of their condition [7, 8], and only 20–25% achieve adequate blood pressure [9] or blood glucose control [10]. Under-diagnosis, under-treatment, and poor control for both hypertension and diabetes are disproportionately high in rural settings [11, 12], where the majority of the Indian population resides.

India’s rural healthcare system is currently organized as a hierarchy of facilities that range from relatively lower-skilled personnel supported by simple infrastructure at the village level to relatively higher-skilled personnel supported by sophisticated infrastructure at the district level. This model attempts to maximize geographical coverage by allowing for “up referrals” and “down referrals” across levels of the healthcare system so that the demand of the individual patient can be met by appropriate resources, such as skilled human resources, infrastructure and services. The referral linkages between these institutions, while theoretically in place, are not implemented efficiently or cohesively. In practice, patients access any level of the healthcare system convenient for them, resulting in a mismatch between patient needs and resource availability. Challenges to the system are compounded by the heterogeneity of treatment guidelines, diagnostic modalities, and medications [13–17] needed at all levels of health care to appropriately serve the growing population with NCDs alongside the large population seeking care for maternal and child health and infectious diseases [18–21].

Recognizing the growing burden of hypertension and diabetes across all segments of the population, the Ministry of Health & Family Welfare, Government of India, has taken the initiative to integrate screening and management of these conditions into primary care under its National Health Mission (NHM) and the National Programme for Prevention and Control of Cancer, Diabetes, Cardiovascular Disease, and Stroke (NPCDCS). A major component of the government strategy is to encourage universal screening for hypertension and diabetes of adults aged ≥30 years in the community and subsequent referral of potential cases to higher level facilities. Consequently, the expected volume of adults seeking care for hypertension and diabetes at government health facilities is anticipated to surge. Building upon the tremendous need and political will to identify optimal and scalable approaches to expand successful care models to manage blood pressure and diabetes within the public healthcare system, we developed the **I**ntegrated **T**racking, **R**eferral, **E**lectronic decision support, and **C**are coordination (I-TREC) program. We describe the components of the I-TREC program and its evaluation design.

## Methods/discussion

### Setting and target population

I-TREC was developed as a collaboration between the All India Institute of Medical Sciences, New Delhi (AIIMS), the Centre for Chronic Disease Control (CCDC), and Emory University. For over a decade, these three institutions have collaboratively developed and tested the combination of information technology (IT), enhanced personnel training, and workflow alterations to improve the quality of care for diabetes and hypertension in diverse settings across India [22–29]. Most of these prior efforts focused on a single level of the healthcare system and relied on research staff to implement the intervention. In I-TREC, however, our goal was to develop and evaluate a coordinated package of tested tools and provider training approaches that catered to functions and personnel available in each type of the 4-tier healthcare system (see Table 1). We further sought to embed the program within the infrastructural scaffolding provided by the Government of India in the interest of future scalability. I-TREC was thus designed to be implemented by personnel and using resources (medications, diagnostics) already present within the public healthcare system.

**Table 1 Tab1:** Intervention components

Healthcare facility level	I-TREC components	Available Staff	Tasks and functions
**Level 1: Village Sub-Centre**	eCRF	ANM	Universal screening of hypertension and diabetes for adults ages ≥ 30 y in the community Enrol community members into the NCD portal Adults with blood pressure ≥ 140/90 or random blood glucose ≥140 mg/dl referred to medical officer at nearest facility (level 2) for confirmation and initiation of treatment
**Level 2: Primary Health Centre**	eCRF+CDSS	SN, MO	Confirmatory diagnosis of hypertension and diabetes of suspected cases referred from sub-centre Routine management of adults with stable hypertension and diabetes Generate and update eCRF Use CDSS to develop treatment plan and determine need for up-referral
**Level 3: Community Health Centre**	eCRF+CDSS	SN, MO	Run dedicated NCD clinics Routine management of adults with stable hypertension and diabetes Generate and update eCRF Use CDSS to develop treatment plan and determine need for up- or down-referral
**Level 4: District Hospital**	eCRF+CDSS	SN, MO	Secondary care available for all health conditions and complications Management of medically complex patients with hypertension and diabetes Generate and update eCRF Use CDSS to develop treatment plan and determine need for up- or down-referral

*ANM* Auxiliary nurse midwife, *CDSS* Clinical decision support system, *eCRF* Electronic case record form, *MO* Medical officer (physician), *SN* Staff nurse

The primary implementation partners for the program include the Department of Health and Family Welfare, Government of Punjab (use of IT tools and altered work flow to deliver routine care); TATA Trusts (conduct training of healthcare workers and technical assistance); and Dell Technologies (development of software and IT infrastructure). Monitoring and evaluation activities for I-TREC will be conducted by AIIMS, CCDC, and Emory University. I-TREC will be implemented in Mukandpur block of Shaheed Bhagat Singh Nagar district, Punjab, India, and evaluated through comparison of program indictors with those observed in the neighboring Sujjon block in the same district (See Fig. 1). The program and comparison locations were selected based on consultation with the Punjab Department of Health and Family Welfare.

**Fig. 1 Fig1:**
[figure not shown]
Geographical location of the study setting. Figure 1 was created by the authors using a map taken from Map Data© 2020 Google

### Program components

Many barriers to optimal hypertension and diabetes care can be alleviated through IT-based quality improvement strategies. Clinical decision support software can provide up-to-date guidance to clinicians [30] to manage hypertension and diabetes following standard treatment protocols. Electronic health records can ensure that access to historical patient data and course of illnesses are available to clinicians to guide clinical decisions at whichever facility the patient enters. IT tools can also help make referral linkages between the different levels of healthcare more transparent, efficient, and effective by suggesting referral thresholds to clinicians, notifying facilities of referred patients, and maintaining a record of recommendations to refer the patient to. Finally, digitized systems to track and monitor case management can incentivize improved health provider performance.

Motivated by the potential benefits IT tools offer clinicians and health systems, the I-TREC program includes: an electronic case record form (eCRF) to consolidate and track patient information; an electronic clinical decision support system (CDSS) for clinicians to provide tailored guideline-based care to patients with in-built prompts for triggering referrals across health facilities as needed; a revised workflow to ensure coordinated care within and across facilities; and enhanced training for clinicians regarding NCD medical content and lifestyle management (See Table 1). Each component of this integrated system is described below.

#### Electronic case record form (eCRF)

The eCRF is the Government of India’s digitized health record focused on compiling patient data relevant to chronic diseases. The eCRF allows nurses to enter patient demographic information, medical history, physical examinations, and laboratory investigations into an electronic form through a web-based “NCD portal.” Patient data are then stored in a cloud server hosted by National Informatics Centre, Government of India. The eCRF ensures that necessary patient medical history will be available seamlessly up and down the healthcare facility hierarchy, reduces redundant data entry when the same patient seeks care at different facilities, and allows clinicians to track patient health information over time across visits. Simultaneously, these data serve as inputs for the CDSS to provide guideline-based recommendations to clinicians to optimize medical and lifestyle management and referral of patients. The eCRF itself was developed by a committee of experts across India, including members of the I-TREC investigator team ([name]). We chose to build upon the Government of India’s eCRF to align our program with the national effort to incorporate IT into the management of NCDs in the public sector.

#### Clinical decision support system (CDSS)

The CDSS generates customized evidence-based treatment advisories for patients with hypertension and diabetes. The treatment advisories are based on up-to-date national and international guidelines that were further vetted by our expert clinical investigators, and tailored to each level of health facility (primary, secondary or tertiary), for example, by taking into consideration the local availability of medications and diagnostic capability. The CDSS algorithms provide the clinician with an instantaneous advisory regarding medication titration based on patient history and current clinical examination as inputted into the eCRF. The attending clinician has the option of rejecting, partially accepting, or fully accepting the advisory to generate a final treatment plan. In addition to the treatment plan, the CDSS has in-built prompts to refer patients up or down the healthcare facility hierarchy to direct patients to the most appropriate level of care for ongoing disease management. The treatment plan, referral instructions, and lifestyle advice specific to the patient become a part of the patient’s eCRF and are also printed out on paper and given to the patient.

#### Healthcare provider training

Healthcare providers employed in both the program and comparison blocks receive refresher content training related to the etiology, behavioral counseling, and medical management of NCDs following established NPCDCS training manuals. The content training is provided over a full day in separate sessions for auxiliary nurse midwives [ANMs], staff nurses, and medical officers. The sessions include training on effective techniques for delivering behavioral and lifestyle advice counselling. Unlike routine training, this refresher training includes innovative learning methods, such as case studies and role playing to enhance trainee engagement to assure improved comprehension and retention of behavioral and lifestyle counselling approaches. In addition, staff nurses and medical officers in the program block receive IT training on the use of the eCRF and CDSS, specific to their level of expertise and the level of healthcare facility in which they are employed.

#### Patient flow under I-TREC

Figure 2 depicts patient flow within and across facilities in the I-TREC program. Following NHM and NPCDCS recommendations, all adults aged ≥30 years are eligible for universal screening of hypertension and diabetes in the community and opportunistic screening in health facilities by government health providers. At the village-level Sub-Centre, the lowest level of the healthcare facility hierarchy, the ANM is tasked with screening adults to identify suspected cases of hypertension and diabetes in the community. ANMs enter screening results into the “ANM portal” using a tablet-based application. Adults who are suspected to have hypertension and/or diabetes are referred to the nearest Primary Health Centre, the second level of the healthcare hierarchy, for diagnosis and treatment (see Table 1 and Fig. 2).

**Fig. 2 Fig2:**
[figure not shown]
Patient flow under the I-TREC program. Panel **a** shows patient flow across facilities and Panel **b** shows patient flow within facilities. Figure 2 was developed by the authors

At Primary Health Centres and above—namely Community Health Centres and the District Hospital—nurses generate and update the patient eCRF through a web-based application on a computer tablet. At the time the eCRF is first generated, nurses record the patient’s clinical history. At future visits, the eCRF is updated with ongoing examination data so that the CDSS is responsive to the patient’s health status at a given visit. Patient data entered into the eCRF are uploaded to a secure cloud-based server once per day, and these data are synced and retrievable at all facilities to inform the CDSS and assist with clinical decisions.

After the initial eCRF review and update by the nurse, patients with confirmed hypertension or diabetes are instructed to see the medical officer, who is aided by the CDSS to manage these conditions. The CDSS algorithms are tailored to the expertise, medications, and diagnostic tests available at each level of facility and customized to the clinical history of the patient over all past and present contacts with the health system. Medically complex patients, such as those who are resistant to therapy, may be referred further “up” the referral hierarchy. The referral algorithms take into account a patient’s full clinical history and current health profile, including the number of medications currently prescribed, treatment response based on laboratory investigations, and comorbidities. For example, if a patient with diabetes under treatment at a PHC has uncontrolled hyperglycemia despite being on the maximum tolerated dose of three oral hypoglycaemic agents, the CDSS will trigger a referral to a CHC. Similarly, if a patient with hypertension under treatment at a CHC level has uncontrolled blood pressure despite being on the maximum tolerated dose of two antihypertensive drugs, the CDSS will trigger a referral to the District Hospital.

Once the patient achieves a stable clinical state, she or he will be referred back “down” to the lowest level of health facility (PHC or CHC) that is suitable for routine management of stable disease and dispensation of appropriate medication.

#### Routine care

Adults residing in the comparator block will continue to receive the usual care by local physicians and nurses using paper-based record systems and without the assistance of the CDSS.

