### Summary

This is the first study in India evaluating the composite impact of a clinical decision support system integrated with the Government of India eCRF, combined with modified patient flow and enhanced healthcare provider training. It is also an important early effort to systematically evaluate a program for integrated management of hypertension and diabetes at all levels of the public healthcare system, starting from the sub-centre up to the district hospital. Lessons learned may inform optimal approaches to improve healthcare processes and health outcomes within the public sector healthcare system in India.

The I-TREC program and its evaluation have several strengths but also some limitations. Given the primacy of scalability, the role of research staff is limited to program design, training, monitoring and evaluation. Therefore, the context and conditions of implementation are beyond the control of investigators. For example, the availability of drugs, diagnostic investigations, and clinicians are likely to impact the reach, effectiveness, and implementation of I-TREC but rest in the hands of the state government. Nevertheless, we expect variations in these structural elements to affect both the program and comparison blocks similarly. In order to maintain comparability between the program and comparison block, neighboring blocks within the same district were chosen. However, this means that both blocks share the district hospital, which will have to be taken into account during the analysis. While we will be able to obtain patient data in the program block from the eCRF, no comparable source of data is available to use in the comparison block. Moreover, undue monitoring of the comparison block may inadvertently lead to compensation behaviors on the part of clinicians that could undermine our ability to measure performance differences across the two blocks. The community survey, in part, is designed to mitigate these limitations by providing a well-designed comparison of healthcare processes and outcomes as observed in the program and comparison blocks.

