### Current status

Intervention development and pre-testing were completed in August 2019. Healthcare providers in both blocks received training in December 2019, and the I-TREC program was launched in January 2020. Prior to the program launch, pre-program data collection, including facility and patient assessments, qualitative research, and community survey, were completed. Since March 2020, both intervention roll-out and research activities have been impacted by the COVID-19 pandemic. Specifically, government healthcare system resources have been diverted from NCD care to test and treat patients with SARS-COV-2, national and local lockdown measures have forced intermittent closures of lower-tier health facilities and prevented field staff from conducting routine monitoring activities. In addition, patient flow through facilities—when open—has generally declined, possibly due to fear of contracting the virus while seeking healthcare. Nevertheless, as and when healthcare facilities are operational, the intervention components are being implemented by nurses and physicians in the program facilities and program monitoring activities are underway. We expect intermittent disruptions to intervention implementation and monitoring activities to continue until the COVID-19 pandemic has been fully controlled.

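### Enhanced training goes to both blocks, so the difference-in-difference estimates the IT and workflow package added to training, not composite I-TREC versus usual care

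*Protocol article*

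**What the plan says.** The Routine care section presents the comparison block as unchanged practice: "Adults residing in the comparator block will continue to receive the usual care by local physicians and nurses using paper-based record systems". It adds that care there is delivered "using paper-based record systems and without the assistance of the CDSS". Training is not mentioned.

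The Healthcare provider training section says: "Healthcare providers employed in both the program and comparison blocks receive refresher content training". It separates this from ordinary practice: "Unlike routine training, this refresher training includes innovative learning methods". Only the IT training on the eCRF and CDSS is confined to the program block. Current status reports that the training took place: "Healthcare providers in both blocks received training in December 2019".

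The Abstract and Program components both list enhanced training as part of I-TREC. The Summary says that the study evaluates the composite impact of CDSS and eCRF "combined with modified patient flow and enhanced healthcare provider training".

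Table 1 assigns eCRF and CDSS to the District Hospital, and Patient flow under I-TREC describes eCRF use and CDSS-triggered referral to it. Health facility and patient assessments counts one hospital common to both blocks. The Summary concedes that "both blocks share the district hospital, which will have to be taken into account during the analysis".

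The Statistical analysis plan section names the program-by-period interaction as the adjusted DiD. The only facility covariate in the printed model is public versus private.

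**The concern.** A component delivered to both groups cannot show its main effect in a contrast between them. The comparator label and the composite claim therefore describe a different comparison from the one the design makes. If results are reported under the present wording, a positive DiD would be credited to a package that includes training, and a null would be read as I-TREC failing to beat usual care. Untrained usual care was not the comparator in either case.

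The shared hospital adds a second difference between label and contrast. Residents of the comparison block may be managed with the CDSS there, and the document does not say how the promised allowance will be made.

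**Working it through.** **Step 1. What each block receives**

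| Element | Program block | Comparison block | Source |
|---|---|---|---|
| Enhanced content training | Yes | Yes | Healthcare provider training; Current status |
| IT training on eCRF and CDSS | Yes | No | Healthcare provider training |
| eCRF and CDSS at the block's own facilities (eCRF only at Sub-Centres) | Yes | No, paper records | Table 1; Routine care |
| Revised workflow | Yes | Not described | Program components |
| District Hospital with eCRF and CDSS | Yes | Shared; handling of comparison residents not stated | Table 1; Health facility and patient assessments; Summary |

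**Step 2. What the interaction estimates**

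Let S be the secular change, T the main effect of content training, P the effect of the IT and workflow package, I any training-by-package synergy, and D the effect in the comparison block of CDSS exposure at the District Hospital. Take S and T as equal in the two blocks.

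- Program change = S + T + P + I
- Comparison change = S + T + D
- DiD = P + I − D

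T drops out. The article does not say whether the baseline survey came before the December 2019 training; it says only: "Prior to the program launch, pre-program data collection, including facility and patient assessments, qualitative research, and community survey, were completed". If the survey came after the training, T is already present at baseline in both blocks and appears in neither change, so the DiD is the same. If it came before, the comparison block's change contains T and is not a pure usual-care trend.

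**Step 3. The plan's sample size and whether it allows for dilution**

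Inputs, from the community surveys section: effect 5 mmHg, SD 18.5, power 0.80, α 0.05, prevalence 20%, ICC 0.018, 50 adults per village, 10% refusal.

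- Per block, one-sided: 2 × (18.5 × (1.645 + 0.842) / 5)² = 169.3, against the stated 168. Two-sided gives 214.9, which does not match.
- 839 × 0.20 = 167.8.
- Design effect: 1 + 49 × 0.018 = 1.882.
- 839 × 1.882 / 0.9 = 1754.4 per block; doubled, 3508.9, against the stated 3508.

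The stated size reproduces, so this point does not rest on an arithmetic error. The steps cover prevalence, clustering and refusal; none allows for dilution.

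**Step 4. Dilution as an assumed range**

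Let e and c be the shares of program and comparison residents with hypertension who are managed with eCRF/CDSS. If the program acts only through such exposure, the contrast shrinks by the fraction a = c/e, and 5 mmHg becomes 5(1 − a). Neither e nor c is given for this population. The Health outcomes section expects 30% of the local population to use government facilities, so e = 0.30 serves as a rough second case beside full exposure. Power below is on the plan's own basis (two groups of 168, one-sided) and is not the power of the DiD.

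| Assumed attenuation a | Contrast (mmHg) | c if e = 1 | c if e = 0.30 | Power, plan's basis |
|---|---|---|---|---|
| 0% | 5.0 | 0% | 0% | 80% |
| 10% | 4.5 | 10% | 3% | 72% |
| 20% | 4.0 | 20% | 6% | 63% |
| 30% | 3.5 | 30% | 9% | 54% |

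Large values of c are not credible when e is small. At e = 0.30, c = 20% would need two-thirds (0.20/0.30) of the comparison block's government users to be CDSS-managed at a hospital that Table 1 reserves mainly for complex cases.

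**The case against.** The best defence is that sharing the content training is an openly stated design choice and a sensible one, because it isolates the IT and workflow package. The DiD is valid for that contrast, and the analysis section defines it by block without claiming more. All of this stands. The fault lies in the comparator label and in the composite claim, which do not match the design.

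The hospital sharing is disclosed, and its handling could be left to a fuller analysis plan that is not shown. That also stands, so the hospital is the lesser part of the point. However, the article prints its model, and the public/private term cannot meet the stated need, since the District Hospital and the blocks' own government facilities are all public.

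A reader might draw four stronger conclusions that the documents do not support:

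- *The DiD is uninterpretable.* It targets a narrower effect, and the hospital dilutes that effect without making it inestimable.
- *Training contributes exactly nothing.* This needs additive effects and equal benefit in both blocks. Synergy between training and CDSS would stay in the DiD.
- *Comparison residents certainly receive the program at the hospital.* No passage says how they are handled there. The Background's remark that patients use whichever level suits them makes exposure plausible, not established.
- *A null would show that training worked in both blocks.* The plan examines change in each block, so a common improvement would be visible, but it could not be separated from secular trend.

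**Conclusion.** The point holds as one of labelling and estimand. As designed, the DiD estimates the added effect of eCRF, CDSS, IT training and revised workflow over usual care plus enhanced content training, including any synergy with training. It does not estimate composite I-TREC against usual care. This follows from the shared training alone and does not depend on the order of survey and training. It assumes that the main effect of training is similar in the two blocks.

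The shared District Hospital may reduce the contrast further, towards the null if the CDSS helps. Its size is unknown. The 4.5 and 4.0 mmHg figures only illustrate an assumed 10% to 20% attenuation, and the documents support no specific loss of power.

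**What to change.** **Wording.** Reconcile the Healthcare provider training, Routine care and Summary sections. Describe the comparator as usual care plus enhanced content training. State in the Statistical analysis plan section that the estimand is the added effect of the IT and workflow package, and limit the composite claim accordingly.

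**District Hospital.** Keep the DiD by block of residence as the primary analysis. Do not adjust for or exclude District Hospital users: where a person is treated is decided after the program starts and may be affected by it. Add an endline survey item on whether hypertension or diabetes care was received at the District Hospital or at a program-block facility, and report the answers by block. The facility attended is only a proxy for CDSS use, so label it as such.

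**Sensitivity analysis.** Pre-specify an exposure-scaled estimate: the DiD divided by the between-block difference in eCRF/CDSS exposure. State its assumption, that the program acts only through personal eCRF/CDSS exposure. Workflow changes may break that assumption, and the result is an effect per exposed person, not a corrected community effect.

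**Cost.** A narrower claim, one or two survey items in place before the 36-month endline, and one extra analysis. The repeated survey items and the primary model stay as they are.
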